## Abstract

**Introduction:**

The coronavirus disease pandemic has worsened psychological distress in people experiencing homelessness (PEH). This study evaluates the impact of learning the Bhagavad Gita versus engaging in Kuchipudi dance on reducing psychological distress in PEH in Chennai and Dhanbad, India.

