The Bhagavad Gita offers practical guidance on navigating daily stressors [12]. Within the realm of RSIs, recent studies offer insights into the potential relevance of the Bhagavad Gita’s teachings for psychological well-being among adolescents [13] and individuals coping with chronic illnesses [14]; however, these studies do not encompass a synthesis of empirical data to validate their findings. Recently, Das and Behura proposed that learning the Bhagavad Gita could improve the stress coping abilities of healthcare providers during the COVID-19 pandemic, drawing parallels between their experiences and those of war veterans; however, this study also lacked empirical substantiation [15].

Considering that homelessness also poses significant challenges to human health, including mental health, and our organization’s volunteers had noted that a significant number of PEH had turned to spirituality as a coping mechanism to deal with the mental health challenges brought about by the COVID-19 pandemic, we hypothesized that imparting the teachings of the Bhagavad Gita as a one-time intervention could enhance the psychological resilience of PEH.

This study aims to bridge the knowledge gap concerning the effectiveness of Hindu RSIs in a previously unexplored population—PEH—by evaluating the impact of learning the Bhagavad Gita on reducing psychological distress among PEH. Engaging in Kuchipudi dance practice as a hobby will function as a positive control, while abstaining from stress-reducing activities will serve as the negative control. In other words, the central research question is, what is the impact of learning the Bhagavad Gita on reducing psychological distress among PEH, and how does this compare with the impact of engaging in Kuchipudi dance practice as a hobby? This multi-site parallel-group RCT seeks to comprehensively assess both short and long-term outcomes. Table 1 outlines the research inquiries guiding our study and presents potential interpretations of the anticipated results.

**Table 1 pone.0310795.t001:** Study design.

Question	Hypothesis	Sampling plan	Analysis plan	Interpretation given to different outcomes

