Is learning the Bhagavad Gita better at reducing psychological distress than engaging in a hobby in people experiencing homelessness	The decrease from baselines to immediately post-intervention, delayed post-intervention, and long-term follow-up Kessler psychological distress scale scores will be significantly larger in the Bhagavad Gita group than in the Kuchipudi dance group	54 participants each in the Bhagavad Gita group, Kuchipudi dance group, Both Bhagavad Gita and Kuchipudi dance group, and Control group for 80% power and 5% alpha	Intergroup differences will be analysed by the generalised estimating equation and analysis of covariance with continued practice and religion as covariates. Subgroup analyses will be conducted by stratifying the participants in each group by age, religion (Hindu, Non-Hindu), educational attainment, and employment. Post-hoc power analyses will be conducted to verify the robustness and reliability of the subgroup analyses	If our hypothesis holds true, it would suggest that learning the Bhagavad Gita is more effective at reducing psychological distress than engaging in a hobby for people experiencing homelessness. By conducting subgroup analyses, we will further investigate if the effectiveness of the intervention varies based on age, religion, educational attainment, and employment

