Does learning the Bhagavad Gita provide any added benefit to people experiencing homelessness who are engaging in a recreational activity in terms of reducing their psychological distress	The decrease from baselines to immediately post-intervention, delayed post-intervention, and long-term follow-up Kessler psychological distress scale scores will be significantly larger in the Both group than the Bhagavad Gita and Kuchipudi dance groups	54 participants each in the Bhagavad Gita group, Kuchipudi dance group, Both Bhagavad Gita and Kuchipudi dance group, and Control group for 80% power and 5% alpha	Intergroup differences will be analysed by the generalised estimating equation and analysis of covariance with continued practice and religion as covariates. Subgroup analyses will be conducted by stratifying the participants in each group by age, religion (Hindu, Non-Hindu), educational attainment, and employment. Post-hoc power analyses will be conducted to verify the robustness and reliability of the subgroup analyses	If the reduction in the Kessler psychological distress scale scores is highest in the Both group, it would suggest that learning the Bhagavad Gita combined with engaging in a recreational activity may offer additional benefits in reducing psychological distress among homeless persons compared to learning the Bhagavad Gita group or engaging in a recreational activity alone. This finding would indicate that the combination of the intervention has a more substantial effect on decreasing distress levels

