### Statistical methods

#### Data analysis

All results will be reported in accordance with the CONSORT guidelines to ensure comprehensive and transparent reporting of the trial’s outcomes. Descriptive summaries of baseline characteristics will be presented to provide an overview of the study population. The comparisons will be between each intervention group and the control group, as well as within each intervention group over time. The repeated measures data will be analysed using the generalised estimating equation (GEE) framework. For the analysis of the primary outcome using the GEE framework, robust standard errors will be used to account for correlated data. Pairwise post-hoc comparisons will be conducted to identify specific group differences. To control for the risk of type I error in these multiple comparisons, the Bonferroni correction will be applied. Subgroup analysis will be conducted using analysis of covariance (ANCOVA) or non-parametric ANCOVA [19] depending on the normality of the data; this may include stratification by age, educational attainment, religion, and employment status. Multiple comparisons will also be addressed using appropriate statistical corrections. These may include the Bonferroni correction, Holm’s adjustment, or the Benjamini-Hochberg procedure, depending on the specific comparisons and the number of tests conducted. The data analysis will be conducted using Python 3.9.13. Statistical significance will be set at a two-tailed p < 0.05.

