### Primary analysis

GEE Framework: The primary outcome, psychological distress as measured by the K10 scale, will be analyzed using the GEE framework. Robust standard errors will be used to account for correlated data due to repeated measures. An exchangeable correlation structure will be assumed.Primary Comparisons: Comparisons will be made between each intervention group (Gita, Kuchipudi, and Both) and the control group. Within each intervention group, comparisons over time (pre-intervention, immediate post-intervention, 40 days post-intervention, and 1-year post-intervention) will be performed.Pairwise Post-Hoc Comparisons: Pairwise post-hoc comparisons will be conducted following significant GEE results to identify specific group differences. The Bonferroni correction will be applied to control for the risk of type I error in these multiple comparisons.

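### Gita v Kuchipudi and Both v each single group are planned hypotheses with 80% power at 5%, but the comparison lists omit them and leave them to Bonferroni-corrected post-hoc tests

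*Protocol article*

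**What the plan says.** The question. The abstract states the aim as a head-to-head comparison: "This study evaluates the impact of learning the Bhagavad Gita versus engaging in Kuchipudi dance on reducing psychological distress in PEH". The Introduction gives the central question two halves: the impact of Gita on distress, and "how does this compare with the impact of engaging in Kuchipudi dance practice as a hobby".

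The hypotheses. In Table 1, the second question predicts that the fall in K10 "will be significantly larger in the Bhagavad Gita group than in the Kuchipudi dance group". The fourth predicts that it "will be significantly larger in the Both group than the Bhagavad Gita and Kuchipudi dance groups". Both refer to all three post-baseline measurements. Both are assigned to GEE and ANCOVA, with no preliminary test and no correction of alpha. For both, the sampling plan gives 54 per group in all four arms, ending "and Control group for 80% power and 5% alpha".

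The analysis. The Primary analysis section defines its comparisons thus: "Comparisons will be made between each intervention group (Gita, Kuchipudi, and Both) and the control group". It adds changes over time within each intervention group. The Data analysis section agrees: "The comparisons will be between each intervention group and the control group, as well as within each intervention group over time". Neither list contains a contrast between two active groups.

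The remaining route. The Primary analysis section continues: "Pairwise post-hoc comparisons will be conducted following significant GEE results to identify specific group differences". Bonferroni is then applied. The Data analysis section has the same pairwise step and correction, but does not make the step conditional on a significant result. Neither section says how many tests the correction covers.

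**The concern.** Table 1 treats the contrasts between active groups as planned and directional, tested at 5%. Under the two analysis sections they can enter only as corrected post-hoc tests, in one of those sections behind a significance gate. The plan thus gives the same contrasts two different statuses and two different alphas.

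Two things are at stake. First, the comparison that answers the second half of the central question is missing from the list of primary comparisons. A reader of the results could not tell whether a Gita v Kuchipudi finding is confirmatory, or at what error rate it was tested. The gate could also stop a planned hypothesis from being tested at all. Second, the power stated for these contrasts belongs to a single test at 5%, not to the test that the analysis sections describe.

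**Working it through.** **Inputs.** From Sample size calculation: two-sided alpha 5% (1.96), power 80% (0.84), difference 7 points, correlation 0.5, four measurements, 54 per group, and 64 recruited per group to allow for dropout. From Data analysis and Primary analysis: Bonferroni, number of tests not stated. The documents give no SD.

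**1. The plan's own figure.**
- Effective size: 55/(1 + 3 × 0.5) = 55/2.5 = 22.0; the plan prints 22.5.
- With the printed 22.5: (1.96 + 0.84)² × 22.5/(7² × 0.5²) = 7.84 × 22.5/12.25 = 14.4; the plan prints 53.3.
- The formula has no outcome SD and uses n to obtain n.

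The 54 per group therefore does not reproduce, so the 80% can only be taken as the plan's own claim.

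**2. Relative loss, taking 80% at 5% as given.** The implied standardised effect is 1.960 + 0.842 = 2.802. Power at a Bonferroni alpha of 0.05/m is Φ(2.802 − z), with z the two-sided critical value. The family size m is my assumption.

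| m | What it would be | Alpha | z | Power at 54 per group | n per group for 80% |
|---|---|---|---|---|---|
| 1 | As stated | 0.05 | 1.960 | 80% | 54 |
| 3 | Three active pairs, one time | 0.0167 | 2.394 | Φ(0.408) = 66% | 73 |
| 6 | All pairs of four groups, one time | 0.0083 | 2.638 | Φ(0.164) = 57% | 84 |

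The last column is 54 × ((z + 0.842)/2.802)², rounded up. Even if all 64 recruited per group stayed in the trial, power would be 74% with three tests and 66% with six.

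**3. Absolute power for assumed SDs.** This is a simple comparison of two means at one time with 54 per group: Φ(7/(SD × √(2/54)) − z), where √(2/54) = 0.1925.

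| Assumed SD | 5% | 0.05/3 | 0.05/6 |
|---|---|---|---|
| 8 | 99.5% | 98% | 97% |
| 10 | 95% | 89% | 84% |
| 12 | 86% | 74% | 65% |

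On this calculation, 80% at 54 per group corresponds to an SD of about 13. Whether the corrected test falls below 80% depends on an SD that the plan does not give.

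**The case against.** **The contrasts are pre-specified in Table 1.** This is true. Table 1 gives them a direction and an analysis method without a gate, and the analysis sections never name them as post-hoc. Their post-hoc status follows only because both comparison lists omit them and the pairwise step is the only one left. That makes this a conflict between Table 1 and the analysis sections; it does not show that the sponsor decided to downgrade the contrasts.

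**The central question is not lost.** This also stands. Gita v control is listed and addresses the first half of the question, and Kuchipudi v control checks the positive control. Only the second half is missing.

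**The comparisons with control might look uncorrected.** A reader might infer that Bonferroni covers only the post-hoc pairs, so that nine comparisons with control (three groups, three times) run at 5% each. With a correlation of 0.5, simulation then puts the chance of at least one false positive at about 29%. The documents do not establish this. The correction follows a pairwise step meant to identify group differences, which can equally include control. The two readings also exclude each other: a family of six pairs already contains the three control pairs.

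**The power loss might be larger, or nil.** Correcting six pairs at three times would take the stated 80% to about 42%, but nothing in the plan says that the family is that large. Conversely, at an assumed SD of 8 or 10, power with six tests stays above 80%. Both remarks are fair. They show that the size is open; they do not remove the mismatch in alpha.

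**Conclusion.** The point holds as an internal conflict and a misattributed power figure. Gita v Kuchipudi and Both v each single group are stated hypotheses in Table 1, yet they appear in neither list of comparisons and are left to corrected post-hoc tests. The 80% at an uncorrected 5% is not the power of those tests. This part needs no assumption about the SD.

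The size is conditional. If the plan's 80% is accepted, power is about 66% with three corrected tests and 57% with six. The absolute shortfall is unknown: no SD is stated, the 54 does not reproduce, and the number of corrected tests is left open. The documents do not support calling the trial underpowered for these contrasts, its central question abandoned, or its comparisons with control free of error control. Whether Bonferroni reaches the control comparisons is ambiguous, and the plan should say.

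**What to change.** - In Data analysis and Primary analysis, add Gita v Kuchipudi to the planned comparisons, and Both v each single group if these are meant as confirmatory. Estimate them from the GEE without requiring a significant overall result first. The comparisons with control can stay.
- Define one Bonferroni or Holm family. Say which contrasts it covers, including whether those with control belong to it, and which follow-up times.
- Restate the power in Table 1 and Sample size calculation at the resulting alpha, from a stated SD and a calculation that reproduces. Otherwise, remove the claim of 80% at 5% for these contrasts.
- Make Table 1 and the two analysis sections agree on the status of each contrast.

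The cost is wording and a less favourable stated power. No arm, visit or measurement changes. Keeping 80% at the corrected alpha by enlarging the trial would be a separate decision for the sponsor.

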### Subgroup analyses

ANCOVA/Non-Parametric ANCOVA: Subgroup analyses will be conducted using ANCOVA or non-parametric ANCOVA depending on the normality of the data. Subgroups may include stratification by age, educational attainment, religion, and employment status.Multiple Comparisons: To address the risk of type I error due to multiple comparisons, appropriate statistical corrections will be applied, which may include the Bonferroni correction, Holm’s adjustment, or the Benjamini-Hochberg procedure.

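### Plain Bonferroni is fixed for the pairwise group contrasts, where Holm would give the same family-wise control with somewhat more power

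*Protocol article*

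**What the plan says.** The Data analysis section, under Statistical methods, plans pairwise post-hoc comparisons between groups and adds: "To control for the risk of type I error in these multiple comparisons, the Bonferroni correction will be applied". The Primary analysis section of the SAP repeats the commitment ("The Bonferroni correction will be applied to control for the risk of type I error in these multiple comparisons") and makes the step conditional: "Pairwise post-hoc comparisons will be conducted following significant GEE results to identify specific group differences". The comparisons it labels as primary are those with control ("Comparisons will be made between each intervention group (Gita, Kuchipudi, and Both) and the control group") and those over time within each intervention group. Contrasts between two active groups therefore enter these sections only through the pairwise step.

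For subgroups the method is not fixed. The Subgroup analyses section gives type I error as the purpose and refers to corrections "which may include the Bonferroni correction, Holm’s adjustment, or the Benjamini-Hochberg procedure". The Data analysis section lists the same three methods, with the choice "depending on the specific comparisons and the number of tests conducted".

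**The concern.** Table 1 hypothesises that Gita does better than Kuchipudi and that Both does better than either alone. The Introduction makes Gita versus Kuchipudi part of the central research question. Four groups give six pairwise contrasts, so single-step Bonferroni tests each at 0.05/6 = 0.0083. The sample size section claims 80% power for one test at 5%, so any correction reduces power on these contrasts. Holm recovers part of that loss without weakening the family-wise guarantee. The plan already names Holm for subgroups but not here.

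The subgroup wording raises a smaller matter. Bonferroni and Holm control the chance of any false claim. Benjamini-Hochberg controls the expected share of false claims among those made. A reader told only that results were corrected would not know which of the two was controlled.

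**Working it through.** **Inputs.** Four groups, allocated equally; two-sided 5%; 54 per group; 80% power for a 7-point difference (Sample size calculation). No SD is given.

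**The plan's own figure.** The printed formula with the printed inputs gives (1.96 + 0.84)² × 22.5 / (7² × 0.5²) = 176.4 / 12.25 = 14.4 per group. With 55/2.5 = 22 in place of 22.5 it gives 14.1. Neither is the stated 53.3. The claimed 80% is therefore taken below as an assumption that sets the scale, not as a verified figure.

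**Scale.** For 80% power at two-sided 5%, 7 points must equal 2.802 standard errors of a group difference. At 54 per group this is a standardised effect of 0.539, or an SD of about 13 points.

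**Thresholds over six contrasts.** Bonferroni compares every p-value with 0.0083. Holm orders them and compares the smallest with 0.05/6, the next with 0.05/5, and so on: 0.0083, 0.0100, 0.0125, 0.0167, 0.0250, 0.0500, stopping at the first failure. No Holm threshold is below 0.0083, so Holm rejects everything that Bonferroni rejects.

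**Bonferroni power.** The two-sided critical value at 0.0083 is 2.638, so power is Φ(2.802 − 2.638) = Φ(0.164) = 56.5%.

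**Holm power, by simulation** (at least 200,000 four-arm trials per scenario, six contrasts, shared groups allowed for):

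| True means, in points better than Control | Bonferroni, a 7-point contrast | Holm, same contrast |
|---|---|---|
| One active group at 7, or all three at 7 | 56.5% | 59.5% |
| Two active groups at 7, the third at 0 | 56.5% | 61.3% |
| Kuchipudi 3.5, Gita 7, Both 10.5 | 56.5% | 61.7% |
| Gita and Kuchipudi 7, Both 14 | 56.5% | 66% |
| Kuchipudi 7, Gita 14, Both 21 | 56.5% | 76-77% |

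With no true differences, family-wise error is 4.2% under both methods. With all three active groups at 7 it is 2.2% with Bonferroni and 3.2% with Holm. The chance of at least one rejection among the true differences is the same under both (80.6% with all three at 7), because the first threshold is the same.

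**Where the gain vanishes.** In a family of only the three control contrasts, with one real effect, power is 65.9% with Bonferroni and 66.0% with Holm. A smaller SD also limits the gain, since Holm cannot exceed the power of an unadjusted 5% test. At 54 per group and six tests, the most Holm could add is:
- SD 10: 95.3% − 84.1% = 11.2 percentage points
- SD 9: 98.1% − 92.0% = 6.1
- SD 8: 99.5% − 97.2% = 2.3
- SD 7: 99.9% − 99.5% = 0.4

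**Not modelled.** The condition of a prior significant GEE result and the three post-baseline time points are left out. Holm's rejections still include all of Bonferroni's under either, but the percentages would change.

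**The case against.** The strongest objection is that nothing here is wrong. Bonferroni is pre-specified, controls family-wise error and comes with matching simultaneous intervals. That Holm is more powerful can be said of any Bonferroni plan. This stands: the point is an improvement in efficiency and must not be read as a fault in validity.

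A reader might also infer from Table 1's hypothesised ordering that power for neighbouring groups would rise from 57% to 76-77%. The documents do not support that. They state an order but no step size, and this figure needs Both to be 21 points better than Control, three times the 7-point difference the plan calls clinically significant. With the same order in 3.5-point steps, a 7-point contrast gains about 5 percentage points.

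On subgroups, a reader might infer that corrected findings would carry several times the expected error rate. A set-up of 36 tests, 6 of them real at 2.8 to 4 standard errors, gives a chance of any false claim of 16-24% with Benjamini-Hochberg against 4-5% with Holm. Neither that number of tests nor effects of that size appear in the documents. In a subgroup of half the sample, 7 points is only 2.802/√2 = 1.98 standard errors, and the figure for 36 tests is then 8.5% against about 4%. The Abstract presents the subgroup analyses as exploratory, where false discovery rate control is a legitimate choice. The stated grounds for choosing, the comparisons and the number of tests, are not themselves results. What remains is that the rule does not say which method goes with which case.

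**Conclusion.** The point holds as a cheap improvement. For the pairwise contrasts, Holm gives the same family-wise guarantee under the same assumptions and never rejects less. On the assumed scale (six contrasts, 7 points having 80% power unadjusted), the gain for a 7-point contrast is about 3 to 10 percentage points, from about 57% to about 60-66%. It is larger only with very wide separation between groups, and close to nil if few effects are real or the SD is near 7 or 8. The scale rests on a power claim that the plan's own formula does not reproduce. The ranking of the two methods does not depend on it.

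The subgroup point is secondary and optional. It asks for one named method and its error rate, and does not show that the listed methods are unsuitable.

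**What to change.** In the Data analysis and Primary analysis sections, replace the Bonferroni correction with Holm's step-down adjustment over the six pairwise group contrasts, and state that these six form the family. This costs two sentences, no participants and no loss of error control, and is a standard option in Python.

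The downside is that Holm has no simple matching simultaneous confidence intervals. Intervals reported beside Holm-adjusted p-values should be labelled as unadjusted, or given as Bonferroni intervals. In either case an interval and its adjusted p-value can disagree about significance, and the report should say so. If simple simultaneous intervals matter more than the extra power, keeping Bonferroni with that reason stated is defensible.

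Optionally, in the Data analysis and Subgroup analyses sections, name one correction in advance and say whether it controls family-wise error or the false discovery rate.
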